**Fig. 2 Fig2:**
[figure not shown]
Intervention 1 and 2

Intervention 1 – pain assessment

Aim: to reinforce the systematic pain assessment of healthcare workers.Encourage training of healthcare workers on pain assessment using the BESD instrument (assessment of pain in dementia of the German Pain Society) by the intervention nurse [39–41].Individual coaching of healthcare workers (2× per healthcare worker at bi-weekly intervals) on the correct use of the BESD in everyday clinical life in nursing homes and a systematic and structured communication among healthcare workers and between healthcare workers and physicians based on ISBAR [42] and SOAPIER [43]. ISBAR is clinical communication technique (ISBAR: identify, situation, background, assessment, recommendation). SOPIER is a problem-oriented technique whereby the nurse identifies and lists the patient’s health concerns (SOPIER: subjective data, objective data, assessment data, plan, intervention, evaluation, recommendation).

Intervention 2 – pain management

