Sustainability and veracity of the interventions are ensured by following the comprehensive evaluation process based on Dobbins [45] that consists of:assessment of the accuracy between the conducted intervention and the study protocol: 50% of the intervention protocols are tested for compliance with the study protocol based on selected pain management strategies and structured communication skills (ISBAR, SOPIER, prompt initiation of medical prescriptions, usage of non-analgesic pain management strategies) by descriptive analysis.evaluation of operating procedures that are associated with pain managementquestioning of acceptability of the interventions carried out for all health care workers with a scale from 0 (= no acceptance) to 10 (= fully accepted)compliance (adherence) of interventions for all health care workers with a scale from 0 (= no adherence) to 10 (= complete adherence)assessment of the potential for change in clinical practice among healthcare workers with a scale from 0 (= no conversion potential) to 10 (= complete transformation possible)assessment of potential change in the management of pain among health care workers with a scale from 0 (= no change in potential) to 10 (= comprehensive amendment potential)

Pain as primary outcome is measured in all people with dementia in the comparison and intervention groups by means of:pain events per shift and per week;degree of pain intensity per work shift, per week day;pain-free intervals.

Secondary outcome variables will be measured by:frequency of behavioural problems (Neuropsychiatric Inventory NPI [46]);number/dosages of psychotropic drugs;Number/dosages of analgesics.

The documentation regarding the assessment of pain by nurses is always done in duplicate, by a health care worker on different education level. Tertiary outcome variables will be measured by:changes in the assessment of pain by healthcare worker on healthcare assistant level andchanges between the two healthcare worker groups on healthcare assistant level and registered nurse level.

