Hypotheses for primary outcomes are:H_a1_: There is a 20% reduction in pain events over time before and after the intervention and between intervention and comparison groups among nursing home older people.H_a2_: There is a 50% reduction in pain intensity over time before and after the intervention and between intervention and comparison groups among older people.H_a3_: There is a 20% reduction in the duration of pain free intervals over time before and after the intervention and between intervention and comparison groups among older people.

Furthermore the following hypotheses will be explored:There is a difference in the behavioural problems score (NPI) before and after the intervention and between intervention and comparison groups among older people.There is a difference in the psychopharmacological drug numbers/dosage before and after the intervention and between intervention and comparison groups among older people.There is a difference in the numbers/dosage of painkillers before and after the intervention and between intervention and comparison groups among older people.There is a difference in pain assessment over time before and after the intervention and between intervention and comparison groups among nursing home older people.There is still a difference in pain assessment by healthcare workers on assistant level over time before and after the interventionThere is still a difference in pain assessment between healthcare workers on assistant level and registered nurses level over time before and after the intervention.

The sample size used in the trial is determined based on the requirements of event history analyses and multilevel analyses to test the mentioned hypotheses.

Event history analyses: The required number of events for a two-tailed test of individual coefficients within a Cox model with other covariates has been calculated based on the method of Hsieh and Lavori [41]. A total of *n* = 179 people and 121 events are required for a power of 0.8 and a significance level of 0.05 based on an expected hazard ratio of 0.6 (SD 0.5), a probability of occurrence of 0.75 and a drop-out rate of 10%. Both the number of people and the number of events determined in the intended study protocol can be collected.

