**Fig. 3 Fig3:**
[figure not shown]
Time schedule

The actual data collection will be done by a study nurse with a BSc in Nursing. Potential confusions/problems with the raw data are discussed within the respective healthcare institution and with the leader of the study. Ambiguities with the procedure of data collection are discussed with the head of project management within the research team who also keeps a research diary. The study nurse transfers the anonymised data to the project management after the third measuring cycle. Two other study nurses enter the data into SPSS and carry out data cleansing before proceeding with the data analysis. The data of the comparison group are disclosed to the project management “PID” in encrypted form by the project manager “ZULIDAD”.

Data analysis will be performed using the IBM software programme SPSS® (version 24). The socio-demographic data are analysed descriptively (frequencies, central tendencies, standard deviations) and the outcome variables as follows:Pain intensity, duration and pain-free intervals are investigated in all dementia patients of the comparison and intervention group measuring the average duration of pain events per work shift (each work shift lasts 8.25 h) and per weekday, and the average degree of pain intensity per work shift, per work day as well as the duration of pain-free intervals with multilevel and events history analyses based on the data observation intervals T0, T1, T2.For the multilevel analyses (linear mixed models) over time, two levels are considered: the dementia patient and the healthcare institution. The event history analyses use cluster-adjusted Cox regressions. Furthermore, event history analyses will focus on evaluating the influence of the two nursing professional groups (at assistant/secondary and tertiary level), the pain pharmacotherapy (number and dosage), behavioural problems (NPI) and the psychopharmacotherapy (number and dosage).

A change in the assessment of pain by the healthcare workers is checked with interrater reliability tests. By means of the interrater reliability test, a potential variation between the two nursing groups on assistant/secondary and tertiary level is monitored.

To ensure the quality of data analyses, each data analysis step is independently checked by three different people.

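### Interrater reliability is compared across cycles while pain itself is expected to fall, so ICC or kappa can change without any change in rating skill

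*Protocol article*

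**What the plan says.** The data-analysis part of the Methods section states the method: "A change in the assessment of pain by the healthcare workers is checked with interrater reliability tests". By the same test, "a potential variation between the two nursing groups on assistant/secondary and tertiary level is monitored". The coefficient is not named.

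The comparison runs over time. The last exploratory hypothesis asks whether there is still a "difference in pain assessment between healthcare workers on assistant level and registered nurses level over time before and after the intervention". Pain is recorded in three cycles, T0, T1 and T2.

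The paired ratings come from routine documentation: "The documentation regarding the assessment of pain by nurses is always done in duplicate, by a health care worker on different education level". The outcome paragraph of the Methods section ranks change in assessment as tertiary, whereas the last paragraph of the Background lists differences between staff groups among the secondary outcomes.

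The primary hypotheses state what the intervention should do to pain: H_a1, "There is a 20% reduction in pain events over time before and after the intervention", and H_a2, "There is a 50% reduction in pain intensity over time before and after the intervention".

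**The concern.** A reliability coefficient does not measure rater error alone. An ICC sets the true spread of pain against true spread plus error. Kappa corrects observed agreement for chance agreement, which depends on how common pain is. If the intervention works as H_a1 and H_a2 expect, both the spread and the prevalence of pain are likely to differ between T0 and the later cycles. The coefficient can then move although assistants and registered nurses disagree by as many points as before.

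What is at stake is the reading of the staff-level result. A lower coefficient after training could be taken as worse agreement when residents simply had less pain. For kappa, a rise could be taken as a training success for the same reason. Naming ICC or kappa later in an analysis plan would not remove the problem, because both have this dependence.

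**Working it through.** The documents give no figure for the interrater analysis, so there is none to reproduce. From the protocol article come the expected falls (50% in intensity, 20% in events) and the 19–83% range for pain in people with dementia (Background). All variances, sensitivities and specificities below are assumptions.

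**1. ICC when scores halve.** ICC = Vb / (Vb + Ve), where Vb is the variance of true pain between residents and Ve the error variance of one rating. If every true score halves, Vb falls to Vb/4. With Ve held at 1:

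| Vb before | ICC before | Vb after | ICC after |
|---|---|---|---|
| 1.5 | 1.5/2.5 = 0.60 | 0.375 | 0.375/1.375 = 0.27 |
| 2.25 | 2.25/3.25 = 0.69 | 0.5625 | 0.5625/1.5625 = 0.36 |
| 4 | 4/5 = 0.80 | 1 | 1/2 = 0.50 |

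In every row the SD of the paired difference is √(1 + 1) = 1.41 points before and after. Disagreement in points has not changed.

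**2. How far this depends on constant error** (middle row):
- Error variance falls with the mean (Ve = 0.5): 0.5625/1.0625 = 0.53, still below 0.69.
- Error SD halves with the score (Ve = 0.25): 0.5625/0.8125 = 0.69, no change.

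**3. Kappa when pain becomes rarer.** Two independent raters each have sensitivity and specificity 0.85. Observed agreement is 0.85² + 0.15² = 0.745 at any prevalence p. The share rated as pain is q = 0.85p + 0.15(1 − p), chance agreement is pe = q² + (1 − q)², and kappa = (0.745 − pe)/(1 − pe). For p = 0.30: q = 0.36, pe = 0.5392, kappa = 0.2058/0.4608 = 0.45.

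| Share of ratings with pain at baseline | Kappa | With 20% fewer | With 50% fewer |
|---|---|---|---|
| 19% | 0.37 | 0.33 | 0.25 |
| 30% | 0.45 | 0.41 | 0.33 |
| 83% | 0.35 | 0.46 | 0.48 |

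Kappa falls from a low baseline prevalence and rises from a high one. The 19% and 83% are prevalences among people, used here only as plausible ends for the share of ratings.

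**4. A bounded scale.** In a simulation of integer scores from 0 to 10 (mean 3, error SD 1, 400,000 pairs), halving true pain moved the ICC from 0.80 to 0.51 and kappa at the BESD cut-off of 2 from 0.44 to 0.32. Exact agreement rose slightly, from 0.29 to 0.32, with the same underlying rating error. Differences in points are therefore much steadier than the coefficients, but not immune near zero.

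**The case against.** **The coefficient is not fixed, and the choice may belong to an analysis plan that is not shown.** This is true of the coefficient. But the article does fix the type of measure and its use across cycles, and both usual choices share the weakness. Raw percentage agreement is much less affected, but it would be an unusual reading of a reliability test.

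**The size is assumed.** This stands. No variance or prevalence of ratings is given, the 50% is a hypothesis, and the ICC effect vanishes if error shrinks in proportion to pain. The figures show that the artefact can be large, not that it will be.

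**Timing.** Intervention 1 concerns assessment and Intervention 2 management, so most of the fall in pain may come late. H_a2 does not say when the 50% is reached. This limits what can be said about T1; it does not help a comparison of T0 with T2.

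**Low stakes.** The outcome is exploratory, no decision rule hangs on it, and pain intensity by cycle will be reported anyway. This lowers the weight of the point. Showing pain levels elsewhere warns a careful reader but does not separate the two explanations.

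**A stronger reading.** A reader might infer that the intervention makes the two raters share scores, which would raise agreement artificially, since Intervention 1 coaches "a systematic and structured communication among healthcare workers and between healthcare workers and physicians based on ISBAR". As pure arithmetic, if 30% of second ratings were copies, 0.69 would become 0.3 + 0.7 × 0.692 = 0.78. The documents do not support that inference. The coaching concerns communication in general, nothing says that the second rater sees the first score, and independence of the duplicate ratings is a detail that a condensed article may leave to the full protocol.

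**Conclusion.** The concern holds in a limited form. A reliability coefficient compared over T0, T1 and T2 mixes rating skill with the level and spread of pain, which the intervention is meant to change. With constant rater error and halved scores, the illustrative ICC falls from 0.69 to 0.36 (0.60 to 0.27 and 0.80 to 0.50 for the other starting values). With error shrinking in full proportion it does not move. For kappa even the direction depends on baseline prevalence. All starting values are assumptions.

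The finding reaches the staff-level comparison only, which is tertiary in the Methods section and secondary in the Background. It does not show that the primary pain outcomes are biased, nor that ratings are copied. The change is worth making because the data for a better measure are already planned.

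**What to change.** - For each cycle, make the paired assistant-minus-nurse difference in points the measure compared over time: mean difference, SD of the differences and limits of agreement, with intervals that resample residents (for example a resident-level bootstrap).
- Stratify these by pain level or adjust for it, for instance by the mean of the two ratings in the pair, because differences in points can also shrink near the bottom of the scale.
- Report any ICC or kappa as description only, beside the mean and SD of pain in that cycle.
- As a secondary precaution, confirm in the full protocol that the two duplicate ratings are entered independently.

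Duplicate rating is already planned, so no additional rater is needed. The cost is slightly more analysis and reporting, plus one sentence on independent entry if the full protocol lacks it.

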## Discussion

The aim of the intervention trial is to improve pain management strategies in older people with dementia in nursing homes. We expect clinically significant findings that will help reduce suffering in the sense of “total pain” for people with dementia. The joint intra- and interdisciplinary collaboration between practice and supply-oriented (nursing) research will have both a lasting effect on the efficiency measurement and provide scientifically sound results. Nursing homes will be able to integrate the findings from the intervention trial into their internal quality comparison processes. The potential for improvements that can be directly influenced by the nursing home itself will be discussed. This means that the nursing homes can respond directly and immediately to deficits. Healthcare workers will be trained and the outcomes of the training will be measured by differences in pain management strategies by people with dementia. People with dementia are therefore protected from direct study interventions.

However, frustration and decreased motivation among healthcare workers could be possible due to intensive study training session during intervention 1 and 2. The study will measure these possible effects during the process evaluation.

Nevertheless, specific knowledge of assessing pain in the everyday clinical situation in many differently qualified healthcare worker teams in nursing homes is lacking. The present intervention trial therefore leads to a broadening of perspectives in palliative care and fills an important gap in the palliative care of people with dementia in nursing homes.
